### Sample size

According to the published research and clinical expectations, we estimated the median time from the baseline to early improvement (at least a 20% reduction of HRSD17 score) of scopolamine plus escitalopram is 6.4 days and the four-week remission rate is 92.3%. The median time from the baseline to early improvement of placebo plus escitalopram treatments is 26.5 days and the four-week remission rate is 57.1%. Considering the time to early improvement, which is fitted to an exponential distribution, and assuming a power of 80% with a two-sided significance of 0.01, a minimal sample size of 54 was calculated using survival (time to event) modules. A common method for testing the proportional hazards assumption is to include a time interaction term to determine if the hazard ratio changes over time, since time is often the culprit behind non-proportionality of the hazards. Evidence that the group*time interaction term is not zero is evidence against proportional hazards. Assuming an attrition of 10%, at least 66 participants are planned.

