### Statistical analysis

All collected data will be analyzed using the SAS Statistical Package (version 9.4; (SAS Institute Inc., Cary, NC, USA). The sample characteristics will be compared using chi-square tests for categorical variables, with Fisher’s Z transformation when needed, and t-tests for normal quantitative variables or the Mann–Whitney U test for non-normal quantitative variables.

Efficacy analyses will be based on an intent-to-treat approach, corresponding to the full-analysis set (FAS), comprising all patients assigned to any treatment group and who have a valid baseline assessment of the primary efficacy outcome variables (HRSD17 total scores). Kaplan–Meier survival analyses will be used to calculate the estimated time from the baseline to early improvement. The Cox proportional hazards regression model will be applied to compare the estimated time to early improvement between the three groups, while controlling for covariates such as age, sex, and duration of illness. Secondary analyses will be performed to assess changes from baseline to each visit in terms of HRSD17, YMRS, CGI, and SDS total scores, using a mixed model of repeated measures (FAS, Mixed-Effect Model Repeated Measure model), with treatment as the fixed factor and baseline scores and age as covariates. A *P* value < 0.05 is considered as statistically significant. The statistical analysis protocol is validated before the interim analysis.

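### The trial is sized at a two-sided 0.01 but judged at P < 0.05, and no adjustment across the two doses is named for the primary three-arm comparison

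*Protocol article*

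**What the plan says.** The Sample size section of the protocol article works from two groups. For scopolamine, the median time to "early improvement (at least a 20% reduction of HRSD17 score) of scopolamine plus escitalopram is 6.4 days"; for saline, the "median time from the baseline to early improvement of placebo plus escitalopram treatments is 26.5 days". Times follow an exponential distribution and, "assuming a power of 80% with a two-sided significance of 0.01, a minimal sample size of 54 was calculated". No reason is given for choosing 0.01.

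The Statistical analysis section applies a Cox model "to compare the estimated time to early improvement between the three groups", adds secondary mixed-model analyses, and closes the same paragraph with one rule: a P "value < 0.05 is considered as statistically significant". It gives the Cox comparison no separate level. It does not say whether that comparison is one three-group test or a set of pairwise contrasts, and it names no hierarchy or adjustment across the high and low dose.

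The Monitoring section plans one interim analysis at 40% of the sample and names the O'Brien-Fleming method for type I error there.

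**The concern.** The article prints two significance levels for the comparison on which the trial is sized. A result between 0.01 and 0.05 succeeds under one section and fails under the other, so the choice could be made after the data are seen. The 80% power statement also refers to a criterion that the analysis section does not use.

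The level matters more with three arms. If either dose can be declared effective on its own unadjusted test, there are two chances of a false positive, or three if the doses are also compared with each other. The O'Brien-Fleming method spends error over repeated looks and does nothing about several arms. It also needs one overall level to spend, and the article supplies two.

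**Working it through.** **Inputs.** From Sample size: medians 6.4 and 26.5 days, exponential times, two-sided 0.01, power 80%, minimum 54, planned 66. From Outcomes: 28 days of follow-up. From Randomization: 1:1:1. Assumptions: 54 is the total over three arms, and every patient is followed for 28 days.

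**Step 1: reproduce 54.** For one active arm against saline, n per arm = (z_alpha + z_power)² × (1/p1 + 1/p0) / (ln HR)².

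- HR = 26.5/6.4 = 4.14; ln HR = 1.421; squared, 2.019.
- p1 = 1 − 2^(−28/6.4) = 0.952; p0 = 1 − 2^(−28/26.5) = 0.519; 1/p1 + 1/p0 = 2.977.
- At 0.01: (2.576 + 0.842)² = 11.68, so n = 11.68 × 2.977 / 2.019 = 17.2. Rounded up, 18 × 3 = **54**, the stated figure.
- At 0.05: (1.960 + 0.842)² = 7.85, so n = 11.6. Rounded up, 12 × 3 = **36**.

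Under this formula 0.01 is the level that produces the sample size.

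**Step 2: power per contrast.** Power = Φ(ln HR / √(2.977/n) − z_alpha).

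| n per arm | 0.01 | 0.025 | 0.05 |
|---|---|---|---|
| 18 (54 in all) | 82.1% | 89.5% | 93.7% |
| 22 (66 in all) | 90.1% | 94.8% | 97.1% |

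**Step 3: family-wise error when no arm differs.** With equal arms, two contrasts sharing the saline arm have correlation 0.5. The error is 1 − P(|Z1| ≤ c and |Z2| ≤ c), with c = 1.960 or 2.576. The three-pair and 2-df rows come from 4 million simulated draws. The interim look is left out.

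| Procedure | each test at 0.05 | each test at 0.01 |
|---|---|---|
| Two doses against saline, unadjusted | 9.1% | 1.9% |
| All three pairs, unadjusted | 12.2% | 2.7% |
| One global 2-df test | 5.0% | 1.0% |
| 2-df test first, pairs only if significant | 5.0% | 1.0% |

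The last row is a valid closed test for three groups: if any two pairwise nulls are true, all three arms are equal, so the 2-df test covers every intersection.

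**The case against.** A reader might infer that the plan as written has a family-wise error of 9% to 12% and no control of multiplicity. The article does not support that. Those rates need separate unadjusted pairwise tests with any one counting as success, and the analysis section fixes neither. A single three-group test fits its wording and holds 5.0%. The two-group sizing and the dose-finding aim in the Background make pairwise testing likely, but not certain. O'Brien-Fleming is also a stated type I error provision, though for the interim only. Contrast definitions may sit in the separate analysis protocol that the article mentions, so their absence here is not in itself a fault.

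A reader might also infer that 0.01 was chosen to cover several contrasts. No reason is given, so that is a guess.

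Reproducing 54 is strong support for 0.01, but not proof. At 0.01, other common formulas give 51 (Schoenfeld) or 66 (Freedman) for three arms, and Freedman's gives 54 at 0.025. A hazard ratio taken from the four-week rates, ln(1 − 0.923)/ln(1 − 0.571) = 3.03, gives 54 at 0.05 by Schoenfeld's formula: 26 events / 0.747 = 34.8 for two arms, so 18 per arm. However, the article calls those remission rates and says that it sized on time to early improvement.

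Finally, testing at 0.05 a trial sized at 0.01 loses no power, and the abstract describes pilot work that needs confirmation. Both points are fair. Neither removes the two printed levels.

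**Conclusion.** The contradiction stands whatever formula was used: 0.01 in one section, and 0.05 without exception in the other, for the comparison on which the trial is sized. That part is certain. The size of the error is conditional: about 9.1% if each dose is tested against saline at an unadjusted 0.05, 12.2% if all three pairs are, and 5.0% under a global or gated 2-df test. These figures assume equal arms and normal test statistics, and ignore the interim look. The Cox comparison is taken as primary because the sample size rests on it and the analyses described after it are called secondary. Because the level decides whether the primary result is declared positive, it should be settled before unblinding.

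**What to change.** State one primary level in both the Sample size and the Statistical analysis sections, and name the primary contrasts. Either of two routes would do:

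1. Test each dose against saline at the planned two-sided 0.01. Family-wise error is about 1.9%, and power is about 82% per contrast at 18 per arm. The sample-size statement stands.
2. Run the 2-df Cox test at an overall 0.05, then pairwise contrasts at 0.05 only if it is significant. Family-wise error is 5.0%. Restate the level and the power for the unchanged number, because 80% power at 0.05 corresponds to 36, not 54. The 94% per contrast is before gating and so is an upper limit.

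Under either route, apply the O'Brien-Fleming boundaries to the chosen level, and keep nominal P < 0.05 for secondary outcomes only.

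The cost is wording, with no extra patients. The primary criterion becomes stricter than a bare P < 0.05. If 0.01 is kept, power per contrast falls from about 94% to 82% at 18 per arm, or from 97% to 90% at the full 22 per arm.

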### Monitoring

Standardized terminology will be used to categorize AEs. The number and proportion of each AE will be summarized according to the system organ class and the preferred term. The PDQ-D5 is administered to assess perceived cognitive deficits from the patient’s perspective.

Interim analysis will be conducted when the study sample reaches 40% of the entire sample to re-evaluate sample size, in reference to the therapeutic effect. If the treatment effect is smaller than expected, we may need to increase the sample size. Blindness will be maintained during the interim analysis. An independent statistician, who is separate from the research team, will perform the interim analysis. The O’Brien-Fleming method [23] will be used to control for type Ι errors. Safety analyses will be used to evaluate hazards with the intention of discontinuing the trial to protect the patients. Type, frequency, and severity of AEs are used to assess safety.

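### O'Brien-Fleming bounds alone do not control type I error when the sample size is raised because the interim effect is small; a cap and fixed stage weights are needed

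*Protocol article*

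**What the plan says.** The protocol article, section Monitoring, gives the timing and purpose of the interim: "Interim analysis will be conducted when the study sample reaches 40% of the entire sample to re-evaluate sample size, in reference to the therapeutic effect". The direction of the adaptation follows: "If the treatment effect is smaller than expected, we may need to increase the sample size". On error control it says only: "The O’Brien-Fleming method [23] will be used to control for type Ι errors". It also says "Blindness will be maintained during the interim analysis", and then "An independent statistician, who is separate from the research team, will perform the interim analysis".

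The section Statistical analysis compares time to early improvement between the three groups with a Cox model adjusted for covariates, and adds "A *P* value < 0.05 is considered as statistically significant". It mentions no combination of stages. The section Sample size uses a different level: "assuming a power of 80% with a two-sided significance of 0.01, a minimal sample size of 54 was calculated using survival (time to event) modules".

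No maximum sample size, re-sizing formula, stage weights or range of interim results that permits an increase is stated.

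**The concern.** O'Brien-Fleming critical values are derived for a sequence of looks whose information levels are fixed, or at least do not depend on the observed effect. The stated rule makes the final sample size a function of that effect. If all data are then pooled in an ordinary Cox test and compared with the O'Brien-Fleming value, the null distribution of the statistic is no longer the one behind that value.

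The direction also matters. Raising the sample size after a small effect gives more weight to fresh data exactly when the first-stage data are unhelpful, and that pushes the error rate up. At stake is whether the declared significance level of the primary comparison holds. The problem lies in the method that is named, so it is more than a detail left out.

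**Working it through.** **Inputs from the article.** Interim at 40% of the sample; 66 patients planned, so 0.4 × 66 = 26.4, about 9 per arm. Levels: 0.01 two-sided (Sample size) and 0.05 (Statistical analysis). Power 80%. Median times to early improvement 6.4 and 26.5 days; follow-up 28 days.

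**Assumptions of this check, not in the article.** The information fraction at the interim is 0.4. One active-versus-placebo contrast is tested with a normal statistic. Caps on the sample size are 1.5, 2, 3 and 4 times the plan. The re-sizing rules are those described below.

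**1. The article's own sample size.** With exponential times, HR = 26.5/6.4 = 4.14 and ln HR = 1.421. The 28-day event probabilities are 1 − 2^(−28/6.4) = 0.952 and 1 − 2^(−28/26.5) = 0.519.

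n per arm = (2.576 + 0.842)² × (1/0.952 + 1/0.519) / 1.421² = 17.2, rounded up to 18. Then 3 × 18 = 54, as stated. This is reproduced only to fix what the expected effect means at the interim: a z of (2.576 + 0.842) × √0.4 = 2.16 at the 0.01 design, or (1.960 + 0.842) × √0.4 = 1.77 if the expected effect is read as the one giving 80% power at 0.05.

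**2. Bounds.** Two looks at information 0.4 and 1 give 3.110 and 1.967 for 0.05, and 4.074 and 2.577 for 0.01. With an unchanged sample size they return exactly 0.0500 and 0.0100.

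**3. Error with a changed sample size.** Let z be the interim statistic, R the final size as a multiple of the plan, b1 and b2 the bounds. The type I error is the average over a standard normal z of

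- 1, if |z| ≥ b1;
- otherwise Φ[−(b2√R − √0.4·z)/√(R − 0.4)] + Φ[(−b2√R − √0.4·z)/√(R − 0.4)].

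Example at z = 0 and nominal 0.05. With R = 1 the argument is 1.967/√0.6 = 2.54, so the conditional error is 1.1%. With R = 2 it is 1.967 × 1.414/√1.6 = 2.20, so it is 2.8%. At z = 2 the change goes the other way, from 18.3% to 11.6%. The net result depends on which interim results lead to an increase.

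**4. Results, nominal 0.05, ordinary final statistic.** Flat: R equals the cap for every effect below expectation. Re-sized: R = (expected z / |z|)², held between 1 and the cap. Zone: re-sized only when z lies between half and all of the expected value.

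| Expected effect | Cap | Flat | Re-sized | Zone |
|---|---|---|---|---|
| 80% power at 0.05 | 1.5 | 5.3% | 5.5% | 5.0% |
| | 2 | 5.4% | 5.9% | 5.0% |
| | 3 | 5.5% | 6.2% | 5.0% |
| | 4 | 5.6% | 6.4% | 5.0% |
| 80% power at 0.01 | 1.5 | 5.2% | 5.4% | 4.9% |
| | 2 | 5.2% | 5.6% | 4.8% |
| | 3 | 5.3% | 6.0% | 4.8% |
| | 4 | 5.4% | 6.1% | 4.8% |

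The worst case over any rule is 5.6%, 6.0% and 6.3% for caps of 1.5, 2 and 3, and about 7.0% with almost no cap. At nominal 0.01 the flat and re-sized rules give about 1.1 to 1.4%.

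**5. With fixed weights.** Use √0.4·Z1 + √0.6·Z2, where Z2 comes from second-stage data only. Under the null Z2 is standard normal whatever R is, so the bounds stay valid. Simulation of 4 million null trials gives 0.0501 at nominal 0.05 and 0.0100 at nominal 0.01.

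**The case against.** The strongest reply is that the inflation needs a premise the Monitoring section does not state, namely an unweighted final test. Fixed stage weights use the same O'Brien-Fleming bounds, so naming that method is compatible with a valid analysis, and an article may leave weights, cap and decision range to the full plan. This stands in part. A reader might infer that the trial has no type I error control; the document supports only that the control named is not sufficient by itself. What remains is that the article ties the sample size to the effect, names only O'Brien-Fleming, and describes the final test as an ordinary Cox model.

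The second reply is that the size rests on caps and rules not in the article. This stands, which is why the range above includes no inflation. A cap of 3 or 4 would mean 198 or 264 patients at one centre, so the upper figures are less plausible.

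Three stronger readings are tempting and should not be made:

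- **That the interim contradicts the blinding.** An effect-based decision needs an arm comparison, but the article gives the interim to an independent statistician outside the team. The natural reading is that the team stays blind while that person compares arms.
- **That the increase would be triggered about half the time even if the design is right.** An estimate does fall below its expectation about that often, but the article says only that an increase may be needed. It is not an automatic trigger.
- **That about 9 patients per arm shows inflation.** The small number makes the decision imprecise. It is no evidence on type I error.

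**Conclusion.** Wrong as written, with a modest effect. O'Brien-Fleming bounds alone do not hold the level under an effect-driven increase followed by the ordinary Cox test. At nominal 5%, the flat rule gives about 5.3 to 5.6% and the re-sized rule about 5.5 to 6.4% for caps of 1.5 to 4 (5.2 to 5.4% and 5.4 to 6.1% if the expected effect is the one sized for at 0.01). If increases are confined to between half and all of the expected effect, the result is 4.8 to 5.0%. The article contains no such restriction; it refers to any effect smaller than expected.

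The defect in the stated method is clear. Confidence in its size is medium, because the cap, the re-sizing rule, the final statistic and the way the two active arms enter the test are all assumed.

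**What to change.** Keep O'Brien-Fleming for the stopping boundary and add, before the interim is run:

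1. A maximum sample size and the rule that links the interim result to the new size.
2. One of two protections. Either a final test with stage weights fixed in advance (Cui-Hung-Wang, or inverse normal, with √0.4 and √0.6), which restores 5.0% under any rule; or a pre-specified promising zone outside which the sample size is not raised, with its limits checked for the significance level that will be used.
3. A sentence that only the independent statistician sees the arm comparison. This clarifies the text and does not correct an error.

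The cost is SAP wording. The weighted test loses slight efficiency if the sample is increased. If the sample is unchanged and the interim falls at 40% of the information, it gives the same weight to each stage as the ordinary test. A promising zone gives up increases after very small effects.

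Blinded re-estimation from pooled data is an option only if the sponsor gives up reacting to the treatment effect, which is the stated purpose of this interim.

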## Discussion

With the high morbidity and high risk of depression, we urgently need to explore antidepressant drugs that can be effective in the short term. Although several previous randomized, controlled studies have examined single scopolamine infusion versus placebo for treatment of unipolar or bipolar depression, all but one showed intramuscular injections of scopolamine to be effective. This is the first randomized, double-blind, controlled trial to systematically investigate the effect of a single intramuscular injection of scopolamine as an adjunct to newly initiated treatment in patients with MDD, with the aim of increasing antidepressant efficacy. This research will open up new areas for the development of antidepressants.

### Trial status

Protocol version 1 (1 February 2017); recruitment start date 15 March 2017; initial submission date 4 September 2017; projected recruitment completion data 31 August 2018.

## Abbreviations

CGI: Clinical Global Impression
CRF: Case report form
DSM-IV: Diagnostic and Statistical Manual of Mental Disorders, Fourth Edition
ECT: Electroconvulsive therapy
FAS: Full-analysis set
GAD-7: Generalized Anxiety Disorder 7-Item
GCP: Good clinical practice
HRSD17: Hamilton Rating Scale for Depression 17-Item
MADRS: Montgomery-Asberg Depression Rating Scale
MDD: Major depressive disorder
NMDA: N-methyl-D-aspartate
PDQ-D5: Perceived Deficits Questionnaire 5-Item
QIDS-SR16: Quick Inventory of Depressive Symptomatology Self Report 16-Item
YMRS: Young Mania Rating Scale
